**LIST OF ABBREVIATIONS AND RELEVANT DEFINITIONS**

|                |                                                                                                                                                                                                                               |
|----------------|-------------------------------------------------------------------------------------------------------------------------------------------------------------------------------------------------------------------------------|
| ABR     | General Assessment and Registration form (ABR form), the application form that is required for submission to the accredited Ethics Committee; in Dutch: Algemeen Beoordelings- en Registratieformulier (ABR-formulier) |
| AE      | Adverse Event                                                                                                                                                                                                          |
| AR      | Adverse Reaction                                                                                                                                                                                                       |
| BAI     | Beck Anxiety Inventory                                                                                                                                                                                                 |
| CA      | Competent Authority                                                                                                                                                                                                    |
| CBT     | Cognitive Behavioural Therapy                                                                                                                                                                                          |
| CCMO    | Central Committee on Research Involving Human Subjects; in Dutch: Centrale Commissie Mensgebonden Onderzoek                                                                                                            |
| CV      | Curriculum Vitae                                                                                                                                                                                                       |
| CEQ     | Credibility/Expectancy Questionnaire                                                                                                                                                                                   |
| DSMB    | Data Safety Monitoring Board                                                                                                                                                                                           |
| EU      | European Union                                                                                                                                                                                                         |
| FAM     | Flight Anxiety Modality questionnaire                                                                                                                                                                                  |
| FAS     | Flight Anxiety Situations questionnaire                                                                                                                                                                                |
| FSQ     | Fear of Spider Questionnaire                                                                                                                                                                                           |
| GCP     | Good Clinical Practice                                                                                                                                                                                                 |
| GDPR    | General Data Protection Regulation; in Dutch: Algemene Verordening Gegevensbescherming (AVG)                                                                                                                           |
| IB      | Investigator's Brochure                                                                                                                                                                                                |
| IC      | Informed Consent                                                                                                                                                                                                       |
| IMP     | Investigational Medicinal Product                                                                                                                                                                                      |
| IMPD    | Investigational Medicinal Product Dossier                                                                                                                                                                              |
| IPQ     | Igroup Presence Questionnaire                                                                                                                                                                                          |
| METC    | Medical research ethics committee (MREC); in Dutch: medisch-ethische toetsingscommissie (METC)                                                                                                                         |
| NEQ     | Negative Effects Questionnaire                                                                                                                                                                                         |
| (S)AE   | (Serious) Adverse Event                                                                                                                                                                                                |
| SPC     | Summary of Product Characteristics; in Dutch: officiële productinformatie IB1-tekst                                                                                                                                    |
| Sponsor | The sponsor is the party that commissions the organisation or performance of the research, for example a pharmaceutical                                                                                                |

company, academic hospital, scientific organisation or investigator. A party that provides funding for a study but does not commission it is not regarded as the sponsor, but referred to as a subsidising party.

**SPQ** Spider Phobia Questionnaire

**SUS** System Usability Scale

**SUSAR** Suspected Unexpected Serious Adverse Reaction

**UAVG** Dutch Act on Implementation of the General Data Protection Regulation; in Dutch: Uitvoeringswet AVG

**VRET** VRET Virtual Reality Exposure Therapy

**VR** Virtual Reality

**WMO** Medical Research Involving Human Subjects Act; in Dutch: Wet Medisch-wetenschappelijk Onderzoek met Mensen

**WSQ** Web Screening Questionnaire

## SUMMARY

**Rationale:** Specific phobias, such as intense fear of flying, heights, or spiders, are the most common forms of mental health disorders worldwide. Specific phobias have a lengthy history of clinical research and very effective treatment for specific phobias using exposure therapy already exist (Wolitzky-Taylor et al., 2008). However, due to high costs, stigma, and long waiting lists, access to evidence-based therapy is currently limited. Meta-analyses on treatment effectiveness for people suffering from specific phobias have shown that Virtual Reality Exposure Therapy (VRET) is as effective as traditional forms of exposure therapy (Marino et al., 2015; Parsons and Rizzo 2008; Powers and Emmelkamp 2008; Opris et al., 2012). VRET, however, involves relatively high costs and limited accessibility, which make it prohibitive for the larger part of the population. This project capitalizes on novel technology and recent scientific advances to develop an affordable treatment modality that is available for anybody, anywhere. Specifically, we will develop and test ZeroPhobia, a self-help VRET for aviophobia and arachnophobia, delivered through a smartphone application (app) in combination with rudimentary cardboard Virtual Reality (VR) glasses. We hypothesize that ZeroPhobia is effective in reducing anxiety symptoms and is user-friendly.

**Objective:** To determine (1) the clinical effects of ZeroPhobia to reduce aviophobia and arachnophobia symptoms at post-test, (2) the clinical effects of ZeroPhobia at 3- and 12-month follow-ups, (3) the user-friendliness of the intervention, (4) if the usage intensity and/or (5) the feeling of presence influence the primary outcome of ZeroPhobia, (6) if exposure or evaluating thoughts mediate anxiety outcomes, (7) if guided VRET results in reduced participant dropout rates, and (8) whether or not ability to fantasize influences the effectiveness of VRET.

**Study design:** This project involves two randomized controlled trial (aviophobia and arachnophobia) with two arms: the intervention condition (ZeroPhobia) and a waitlist control condition.

**Study population:** For aviophobia  $n = 96$  and for arachnophobia  $n = 72$  individuals (18-65 years) who experience aviophobia or arachnophobia symptoms, respectively, will be recruited from the general population to participate in the trial.

**Intervention:** The intervention ZeroPhobia is 6-week self-help VRET for aviophobia and arachnophobia that is delivered through a smartphone application (app) in combination with rudimentary cardboard VR goggles. ZeroPhobia includes modules of psychoeducation, case examples, exposure through VR, cognitive techniques, monitoring of symptoms, and relapse prevention. Participants in the waitlist condition will be offered the intervention directly after post-test.

**Main study parameters/endpoints:** The main study parameters are the post-test differences in phobic anxiety symptoms between the experimental and control condition, and follow-up differences in anxiety symptoms between baseline and follow-up in the experimental condition.

**Nature and extent of the burden and risks associated with participation, benefit and group relatedness:** The burden of participation consists of completing online baseline questionnaires (15 minutes) and performing the intervention (6 modules lasting 5-20 minutes across 6 weeks and daily VR exposure practice from module/week 3 onwards, recommended 10 minutes daily). In addition, participants will be asked to complete an online post-intervention assessment immediately after completion of the intervention (20 minutes) and at follow-up after 3 and 12 months (20 minutes). There is minimal risk involved and the burden to participants is limited.

## 1. INTRODUCTION AND RATIONALE

Specific phobias are intense and irrational fears for a particular object or situation that poses no objective threat (Ledoux, 2015). Think, for example, of fear of spiders, heights, needles, or flying. People with a specific phobia recognize that their fear is excessive and unreasonable, yet they are unable to overcome it. The object or situation causes the person suffering from the phobia to endure intense anxiety and distress, which can significantly interfere with his/her ability to function in their private and working lives. With a lifetime prevalence nearing 10%, specific phobias stand at the top of the cost hierarchy of all mental disorders (Smit et al., 2008). More than 500,000 people in the Netherlands currently suffer from one or more specific phobias and each year there are 75,000 new cases with a specific phobia diagnosis (De Graaf et al., 2010). The estimated annual societal cost of specific phobias is €168 million (Smit et al., 2008). Due to high treatment costs, long waiting lists, and a general reluctance to seek treatment, access to evidence-based therapy is currently limited. Only around 20% of people in the Netherlands with a specific phobia reported having access to treatment (De Graaf et al., 2010). As specific phobia treatment is not covered by health insurance in the Netherlands anymore, the current percentage of people who receive treatment may be even lower. If left untreated, specific phobias can become chronic and increase the risk of developing other mental disorders, such as anxiety and depression. Given the psychological burden phobias carry, along with increased risk of developing comorbid depressive and anxiety disorders and the heavy economic burden for society (Kessler, 2005), there is a need for affordable and scalable self-help interventions.

Specific phobias have a lengthy history of clinical research and very effective treatment already exists (Wolitzky-Taylor et al., 2008). So-called 'exposure therapy' refers to a form treatment in which a person is gradually exposed to the object or situation of his/her fear. Over the past decade, a new type of treatment based on these same principles has emerged making use of virtual reality (VR), rather than exposure 'in vivo'. In virtual reality exposure therapy (VRET), artificially created, computer-generated environments replace in vivo therapy in order to expose clients to their phobia. Meta-analyses on treatment effectiveness for people suffering from anxiety disorders and specific phobias in particular have shown that VRET is as effective as traditional forms of exposure therapy (e.g. Goncalves et al., 2012; Morina et al., 2015; Parsons and Rizzo, 2008; Powers and Emmelkamp, 2008; Opris et al., 2012) in reducing anxiety and other outcomes, such as depression. In a review of 14 studies (Morina et al., 2015), participants receiving VRET for specific phobia improved significantly on behavioral assessments after VRET from pre- to post-test (aggregated uncontrolled effect size  $g = 1.23$ ) as well as when compared with

waitlist control subjects ( $g = 1.41$ ). Furthermore, there were no significant differences between VRET and exposure in vivo at post-test and follow-up ( $g = -0.09$  and  $0.53$  respectively). In another meta-analysis of Opris et al. (2012), results demonstrated that VRET has better outcomes than waitlist controls, similar efficacy between VRET and C(B)T, and no difference in dropout rate between VRET and exposure in vivo. This research shows that virtual environments can be usefully employed as substitutes for real-world settings (Slater et al., 2006, 2013). Aside from demonstrated effectiveness for anxiety disorders and specific phobias in particular, VRET has a number of additional advantages over traditional in vivo treatment, such as the possibility to conduct therapy within the confines of the therapist's office, rather than having to go outside. Furthermore, VRET offers more flexibility in terms of sequencing and intensity of treatment and graduating of exposure. That is, people can practice more often and with a larger variety of scenarios compared to in vivo exposure. In spite of its advantages over traditional in vivo therapy, VRET still involves relatively high costs and limited accessibility which make it prohibitive for the larger part of the population. Existing VRET often also requires heavy graphic processing capabilities not found in ordinary computers and mobile devices. Additionally, existing VRETs still require the intervention of a therapist.

Research into mobile apps as a method to intervene for psychiatric disorders are promising (e.g. Donker et al., 2013; Eysenbach et al., 2011; Saeb et al., 2015). App-based mental health interventions based on e.g. CBT principles have shown to be effective in reducing mental health symptoms with within-group and between-group intention-to-treat effect sizes ranging from  $d = 0.29 - 2.28$  and  $0.01 - 0.48$  at post-test and follow-up, respectively in a review of Donker et al. (2013). Advantages are better accessibility and participant retention, real-time progress monitoring, portability, and flexibility. As far as we know, one study has investigated the effectiveness of VRET using a mobile application for fear of spiders. Results showed a reduction in anxiety levels (Piercey et al., 2012). Another study investigating VRET on a smartphone has recently found VRET to be effective at reducing spider phobia symptoms and non-inferior to traditional one-session exposure therapy (Miloff et al., 2019).

Recently, we have explored the feasibility and efficacy of ZeroPhobia: Acrophobia, a VRET delivered through a smart phone app using Google cardboards for fear of heights (Donker et al., 2019). The randomized controlled trial (RCT) demonstrated large effect sizes and ZeroPhobia: Acrophobia was rated user-friendly. The aim of the proposed project is to test a (similar) low cost, scalable, and evidence-based solution for aviophobia and arachnophobia symptoms through exposure therapy by integrating VR technology with a smart phone app in two separate RCTs. Both interventions will be tested for its effectiveness in reducing anxiety symptoms and user-friendliness. ZeroPhobia: Arachnophobia will differ

from ZeroPhobia: Aviophobia in that it will be a guided VRET, in order to determine whether drop-out rates are lower than previous, unguided trials of ZeroPhobia. The study will be of a randomized controlled trial (RCT) design and will be conducted amongst adults from the general Dutch populations with aviophobia and arachnophobia symptoms.

We hypothesize that both ZeroPhobia applications will effectively reduce anxiety symptoms as well as be rated as user friendly.

## **2. OBJECTIVES**

Primary Objective: To determine the clinical effects (a reduction in anxiety symptoms – aviophobia and arachnophobia at post-test [between the experimental condition and controls]) of ZeroPhobia, and whether effects are sustainable at 3- and 12-month follow-up (a reduction in anxiety symptoms between baseline and follow-up for those in the experimental condition)

Secondary Objective(s): To determine the user-friendliness of ZeroPhobia, if it is effective in reducing depression and anxiety, to determine whether usage intensity and presence in the VR environment influences the effects of ZeroPhobia, to determine whether exposure or evaluating thoughts mediate anxiety outcomes, to determine whether or not guided VRET is related to reduced participant drop-out rates, and whether ability to fantasize influences the effectiveness of VRET.

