## **3. STUDY DESIGN**

A randomized controlled design will be carried out, in which the effectiveness and user-friendliness of an online app-based VR self-help treatment 'ZeroPhobia: Aviophobia' and 'ZeroPhobia: Arachnophobia' will be evaluated. In this study, 96 (aviophobia) and 72 (arachnophobia) participants from the Dutch general population will be randomized in 2 separate RCTs over 2 conditions: the experimental condition (ZeroPhobia: Aviophobia or Arachnophobia) and a waitlist control condition. The duration of the intervention will be 6 weeks. Measures will be taken at baseline, directly after the intervention (6 weeks) and at 3- and 12- month follow-ups. All measures will be completed online. Subjects in the wait-list condition will receive the intervention after completion of the post-test. Randomization (block randomization with 6, 8, 10, and 12 blocks) will be performed by an independent researcher. Figure 1 presents the flow chart of the study.

[figure not shown]

Figure 1: flow chart

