Those who were randomized to the intervention condition will also receive 3- and 12-month follow-up questionnaires. These surveys will include the FAS and FAM (aviophobia) or FSQ and SPQ (arachnophobia), PHQ, BAI, questions about receiving professional treatment for their phobia, and flight usage questions (duration: 20 minutes). Two reminders will be given across two weeks to fill in follow-up questionnaires, the first being an e-mail and the second a phone call. All assessments are programmed with Survalyzer software. For an overview of measurements, see Table 1. If desired, general information about the outcomes of the study will be sent to the participant after completion of the study.

*Table 1: Overview of measures*

| Measures     |                                                                               |          |                |                         |
|--------------|-------------------------------------------------------------------------------|----------|----------------|-------------------------|
|              | Aim                                                                           | Baseline | Post-test (6w) | Follow-up (3, 12 month) |
| Demographics | To determine characteristics of sample                                        | x        |                |                         |
| FAS or FSQ   | To determine symptoms of aviophobia/arachnophobia and treatment effectiveness | x        | X              | x                       |
| FAM or SPQ   | To determine symptoms of aviophobia/arachnophobia and treatment effectiveness | x        | x              | x                       |
| BAI          | To determine symptoms of anxiety and treatment effectiveness                  | x        | x              | x                       |

|                                                   |                                                                                     |   |   |   |
|---------------------------------------------------|-------------------------------------------------------------------------------------|---|---|---|
| PHQ                                               | To determine symptoms of depression and treatment effects                           | x | x | x |
| SUS                                               | To determine program's user-friendliness                                            |   | x |   |

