## **10. STATISTICAL ANALYSIS**

### **10.1 Primary study parameter(s)**

The primary outcome measure (FAS for aviophobia, FSQ for arachnophobia) will be treated as a continuous outcome. Continuous variables will be presented as mean, standard deviation, and minimum and maximum number of observations. Descriptive statistics of demographics and clinical outcomes will be compared between the experimental and control condition. The quantitative analysis of the primary endpoints will be performed on an intention-to-treat basis following the per protocol analysis (PPA) according to CONSORT recommendations and SPIRIT guidelines for reporting results (Chan 2013a, 2013b; Eysenbach et al., 2011). Comparisons will be made between and within the groups for pre- and post-measurement and follow-up. Multiple imputation will be used in dealing with missing data, assuming this is "at random" (Brunton-Smith et al., 2014). We will calculate Clinical Meaningful Change on the FAS (Evans, 1998) and a reliable change criterion (Evans, 1998). We will also calculate the number needed to treat (NNT) based on (Christensen et al., 1986; Cohen, 1972). Standardized effect sizes (Cohen's d) and the confidence intervals are calculated. STATA version 16 will be used for the analyses. The best static analysis procedure to perform the analyses for this RCT will be reviewed before the data is analysed.

Intention-to-treat analysis will be used on continuous scales using repeated measures analysis of variance (ANOVA). Per protocol analysis will be performed by independent sample t-tests. Standardized effect sizes (Cohen's d) and confidence intervals will be calculated. SPSS version 21 will be used for the analyzes. A  $p$ -value  $<0.05$  will be considered to indicate statistical significance.

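### The primary objective judges sustainability at 3 and 12 months by an uncontrolled change from baseline, which shows that some improvement remains, not that the post-test gain is kept

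*Protocol*

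**What the plan says.** The Summary lists two kinds of main parameter: the post-test difference between conditions, and "follow-up differences in anxiety symptoms between baseline and follow-up in the experimental condition". Section 2 puts both in the primary objective and, for the second, asks "whether effects are sustainable at 3- and 12-month follow-up (a reduction in anxiety symptoms between baseline and follow-up for those in the experimental condition"). No section names a contrast between post-test and follow-up, a margin, or a share of the gain that must be retained.

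On who is measured, section 8.3 states: "Those who were randomized to the intervention condition will also receive 3- and 12-month follow-up questionnaires". On the control arm, section 3 states: "Subjects in the wait-list condition will receive the intervention after completion of the post-test".

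On analysis, section 10.1 states, and section 10.2 repeats: "Comparisons will be made between and within the groups for pre- and post-measurement and follow-up". Section 10.1 adds: "Intention-to-treat analysis will be used on continuous scales using repeated measures analysis of variance (ANOVA"). It does not name the contrasts to be taken from that model. The sample size section covers only the experimental-versus-control difference.

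**The concern.** Whether an effect lasts is a question about what happens after post-test. A test anchored at baseline answers a different one: is the score still lower than at entry? The answer can be yes after a substantial relapse. Because the contrast sits in one arm, it also takes in natural course and any other care received, with nothing to set against them.

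The analysis section adds a second difficulty. Read literally, it includes a between-group comparison at follow-up. The schedule collects no waitlist data at 3 or 12 months, and the waitlist is no longer untreated after post-test. At stake is the long-term conclusion: a report could state, as part of the primary objective, that effects were sustained when a good part of them had gone, or could imply a controlled long-term comparison that the design does not provide.

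**Working it through.** **The plan's own figures.** A two-sided t-test at 0.05 with power 0.80 needs 33.02 per arm for d = 0.70 and 25.52 for d = 0.80. Rounded up, these are 34 and 26, as the sample size section states. The totals of 96 and 72 correspond to 68 × 1.4 = 95.2 and 52 × 1.4 = 72.8 (the latter stated as 72). All of this concerns the between-group difference. No figure is given for the follow-up part.

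**Inputs for the illustration.**
- Randomised per arm: 48 and 36 (sample size section).
- Dropout: 40% (same section), leaving 48 × 0.6 = 28.8 and 36 × 0.6 = 21.6, or about 29 and 22.
- Post-test gain within the intervention arm: not in the documents. The planning effects of 0.70 and 0.80 SD, which are between-group values, serve as proxies.
- Correlation between visits, rho: not in the documents. Assumed 0.3 to 0.7, with equal SD at each visit.

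**Smallest observed change from baseline that reaches p<0.05**, in SD units: t(0.975, n − 1) × sqrt(2(1 − rho)/n). The tolerated loss is 1 − (this change)/(gain).

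Aviophobia, n = 28.8, t = 2.049, gain 0.70:
- rho 0.3: 2.049 × 0.2205 = 0.452; loss 1 − 0.452/0.70 = 35%
- rho 0.5: 2.049 × 0.1863 = 0.382; loss 45%
- rho 0.7: 2.049 × 0.1443 = 0.296; loss 58%

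Arachnophobia, n = 21.6, t = 2.082, gain 0.80:
- rho 0.3: 2.082 × 0.2546 = 0.530; loss 1 − 0.530/0.80 = 34%
- rho 0.5: 2.082 × 0.2152 = 0.448; loss 44%
- rho 0.7: 2.082 × 0.1667 = 0.347; loss 57%

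These are thresholds for the observed change. A true residual effect exactly at the threshold would be significant only about half the time.

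**The same question as a probability.** If half of the true gain is lost, the paired test has effect size 0.5 × gain / sqrt(2(1 − rho)). Over rho 0.3 to 0.7, the chance that the baseline-to-follow-up test is still significant is:
- aviophobia: 0.33-0.64 with 28 assessed, 0.52-0.87 with all 48
- arachnophobia: 0.31-0.62 with 21 assessed, 0.51-0.85 with all 36

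**Control data at follow-up.** Under section 8.3, the scheduled waitlist observations at 3 and 12 months are 0 of 48 and 0 of 36. Section 3 gives the waitlist the intervention after post-test, so scores collected later would not come from an untreated group.

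**The case against.** Several points on the other side are sound.

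- **The randomised post-test contrast is untouched.** It is the only powered comparison. Post-test and follow-up scores are both collected, so a relapse would be visible in the data. The baseline-anchored test is not empty either: full relapse would fail it. This limits the damage but does not make the definition in section 2 a test of maintenance.
- **A reader might infer that the protocol firmly plans a controlled long-term comparison.** The text does not go that far. The Summary and section 2 assign between-group comparison to post-test and within-arm comparison to follow-up, and the sentence in 10.1 and 10.2 can be read in that light. It is an ambiguity, but one to close, since its literal reading cannot be carried out. Section 8.3 does say that the waitlist follows the same programme procedure, and the flow chart is not shown, but the statement of who receives the follow-up questionnaires is explicit.
- **A reader might infer that waitlist follow-up scores will be imputed.** Section 10.1 says only: "Multiple imputation will be used in dealing with missing data, assuming this is 'at random". It does not say that visits never scheduled count as missing.
- **A reader might infer a chi-square test of flights between groups at follow-up.** Section 10.2 does not give the time point, and flight questions are also asked at post-test, where both arms are assessed.
- **A reader might infer that regression to the mean inflates the result.** That depends on whether the screening score serves as baseline. The baseline list in section 8.3 omits the FAS and FSQ, while section 11.2 and Table 1 include them at baseline. With a fresh baseline, much of the regression would fall before it. It is a possibility, not an established bias.
- **Other care** is recorded at post-test and follow-up so that it can be controlled for (section 8.1.3).
- **A reader might infer an inflated error rate from several primary tests.** Nothing says that any one of them suffices for success, the two follow-up tests share participants and baseline, and asking whether effects last presupposes a post-test effect.

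The analysis plan may name contrasts, and section 10.1 foresees a review of the procedure before analysis. But the protocol itself fixes the definition of sustainability, and that definition is what needs correcting.

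**Conclusion.** The point holds. The follow-up part of the primary objective is defined by a one-arm change from baseline, which cannot show that the post-test gain was kept. At the protocol's planning effects, an observed loss of about 35-58% (aviophobia) or 34-57% (arachnophobia) is compatible with p<0.05. These figures rest on 40% dropout, on between-group effects used as proxies for the within-arm gain, on constant SD and on an assumed rho of 0.3 to 0.7; they illustrate and do not predict. A reader might conclude that most of the gain could routinely vanish unnoticed. That would need a larger gain or a higher correlation than the documents support as a general statement.

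There is no untreated comparison at 3 or 12 months, and sections 10.1 and 10.2 should not leave room for one. The primary post-test comparison is unaffected.

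**What to change.** In the Summary and section 2, keep the between-group post-test difference in FAS or FSQ as the primary test. For 3 and 12 months, define maintenance as the change from post-test to each follow-up in the experimental arm, estimated with a 95% CI. Report the change from baseline to follow-up as uncontrolled and descriptive.

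In sections 10.1 and 10.2, state that between-group comparisons, including those of flights taken, apply to post-test only, and that unscheduled waitlist follow-up values are not imputed.

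The data needed are already in the schedule, so the change is wording only. The price is a more modest long-term claim: how much of the gain was kept in the treated arm, without a controlled long-term effect.
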